## Discussion

3.

Current SSI prevention practice in UK Vascular surgery varies considerably, with little consensus on many measures (15). SSI prevention guidelines recommended by international bodies (12–14), include over 15 generic methods of preventing SSIs. Some of them are supported by evidence from randomized control trials (RCTs), such as avoiding razors for preoperative hair removal and the decolonization with intranasal antistaphylococcal agents for high-risk procedures. Both methods have been shown to reduce the SSI rate. The use of the WHO surgical checklist leads to a lower SSI rate after its implementation. The exact mechanism of this is suspected to be multifactorial (6). Multiple guidelines (12–14) recommend using antiseptic skin agents, though specific recommendations vary. Using alcohol-based chlorhexidine reduces the risk of SSI compared with aqueous iodine (24). Body surface warming systems to maintain normothermia perioperatively have strong evidence in preventing complications of hypothermia and lowering SSI rates (25). Postoperative negative pressure wound therapy decreases SSI rates in vascular surgeries but was not associated with a statistically significant decrease in SSI rates in other surgical disciplines (6). Antibiotic prophylaxis is recommended by all guidelines (12–14), RCTs focusing on vascular surgery demonstrated a significant reduction in SSI rate (26, 27). Although there are no RCTs on the effect of perioperative glycemic control and its impact on SSI rates, this is recommended in all major guidelines (6, 12–14). Retrospective studies do however confirm a higher risk of SSI rates in patients with postoperative hyperglycemia (6).

The incidence of SSI varies across surgical procedures, specialties, and conditions. Diagnostic and reporting challenges make true SSI rates difficult to capture. SSI rates are reported to vary from 0.1% to 40%. There are several patient- and procedure-related factors that influence the incidence of SSI. Patient comorbidities, advanced age, frailty and surgical complexity can increase the risk of developing an SSI. Additionally, prolonged duration and classification of the surgery are important procedure-related factors (28).

Given the inconsistency in guidelines on how to prevent SSIs, there is a need for standardization. This survey will investigate the disparity in SSI preventative measures between different surgical fields and countries. It will ascertain whether surgeons could feasibly participate in recruiting to platform randomized controlled trials assessing multiple interventions, including antibiotic prophylaxis.

### Limitations

3.1.

Reminders will be sent on a 2-weekly basis to increase the response rate and to prevent sampling bias. Additionally, the study will be advertised on its own Twitter account to gain attention. Response fatigue is a common issue, leaving some questions unanswered. To keep this to a minimum, the survey has been designed to only ask relevant questions and to be succinct, clear, and unambiguous.

Due to the nature of the study, there is room for responder and recall bias. To minimize this, questions wording and survey length have been considered carefully during all steps of the development of the survey. Questions will be categorized into SSI-related preoperative, perioperative, and postoperative themes to preserve the structure and enable ease of organization for respondents to follow.

Additionally, there may be discrepancies in the response rates between different countries, not providing an accurate representation of certain regions. There may also be different local/national guidelines and unequal access to certain resources depending on the geographical regions. As this survey will be delivered worldwide, questions are based on guidelines from the National Institute for Health and Care Excellence (NICE), Centers for Disease Control and Prevention (CDC) and World Health Organization (WHO). These guidelines are internationally recognized and available, therefore discrepancies between geographical regions and differences in local guidelines should be kept to a minimum.

There is no standardized consensus recommendation on SSI prevention regarding perioperative practice. Unsurprisingly this can lead to a discrepancy in clinical practice, as shown by a questionnaire study within the UK (15). If international and pan-surgical SSI prevention practices also vary, guidance recommended by international bodies is not being followed. This may be due to the lack of underlying evidence for SSI prevention practice, and thereby the necessity for high-quality RCTs to establish the best practice for patients and surgeons worldwide.

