In recent years, guidance on the prevention of SSI has been published by key organizations; National Institute for Health Care and Excellence (NICE), Centers for Disease Control and Prevention (CDC) and the World Health Organization (WHO) (12–14). However, a national survey of UK Vascular surgeons conducted by our group identified disparity in recommendations across these guidelines, which was noted to be due to the lack of underlying evidence (15). This study found variability in SSI prevention practices across different institutions, as well as a lack of relevant registries, clinical perception and literature data for SSI rates (15). This follow-on survey aims to assess the barriers in establishing uniform practice including the development of registries. As wound infections can occur after every type of surgery, wherever in the world it may take place, the steering committee of the current project decided to disseminate the follow-on survey to surgeons from all specialties internationally.

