### Objectives

2.1.

Primary objective:
-To identify the barriers to establishing standardized SSI prevention practice.Secondary objectives:
-To identify intra- and inter-specialty variations in surgical site infection prevention practice.-To identify variations in practice amongst financial systems such as state and privately funded healthcare systems and economical classifications.

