### Questionnaire development

2.3.

A pilot questionnaire will be developed based on SSI prevention measures outlined in the CDC (2017), WHO (2018), NICE (2019), Wounds UK (2020) and the International Surgical Wound Complications Advisory Panel (ISWCAP) guidelines. Additionally, feedback from the survey of surgical site infection prevention practice in UK vascular surgery will be used to inform survey questions/design (12–14, 18, 19). Since the survey will be targeting participants across multiple specialties, it will only contain general prevention measures widely applicable. A draft survey will be provided in Supplementary Material 1.

The questionnaire will be structured into five sections; demographics, SSI surveillance, preoperative, peri-operative and postoperative SSI prevention domains. Data will be collected on participant surgical specialty, operative grade, country of practice and financial healthcare system of practice. SSI data will include criteria used for diagnosis. There were 15 perioperative domains formulated the UK questionnaire, which will be scrutinized against the CDC, WHO, NICE and ISWCAP guidelines outlined above by the SSC, to form a pilot questionnaire. The process of questionnaire development will be carried out through discussion by members of the SSC and a record of any question refinement will be documented. The number of questions will not be rigidly defined but the SSC will consider the impact on survey duration which can influence completion rates.

The pilot questionnaire will be distributed to at least two consultants of each surgical specialty; vascular, general, orthopedic and trauma, urology, plastic and reconstructive, cardiothoracic, neurosurgery and otolaryngology for multiple rounds of validation. After each round feedback will be analyzed by the SSC and consensus-based changes will be adopted. Any alterations will be done so on unanimous decision and documented as major (questions removed or added), and minor (wording alterations). The survey will be validated further in subsequent rounds until the SSC agrees no further alterations are required.

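### Drawing questions from NICE, CDC and WHO guidelines does not keep regional and local-guideline differences to a minimum, and variation should not be read simply as non-adherence

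*Protocol article*

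**What the plan says.** The Limitations section (3.1) first concedes the problem: "There may also be different local/national guidelines and unequal access to certain resources depending on the geographical regions". It then notes that the questions rest on NICE, CDC and WHO guidance and concludes: "These guidelines are internationally recognized and available, therefore discrepancies between geographical regions and differences in local guidelines should be kept to a minimum". The following paragraph says that if practice proves to vary across countries and specialties, the advice of the international bodies is not being adhered to. It offers weak underlying evidence as a possible reason.

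Other sections bear on this:
- The Introduction reports that the group's earlier UK vascular survey "identified disparity in recommendations across these guidelines, which was noted to be due to the lack of underlying evidence", referring to NICE, CDC and WHO.
- The Discussion says "Multiple guidelines (12–14) recommend using antiseptic skin agents, though specific recommendations vary" and draws the study's rationale from this: "Given the inconsistency in guidelines on how to prevent SSIs, there is a need for standardization". It adds: "This survey will investigate the disparity in SSI preventative measures between different surgical fields and countries".
- Objectives (2.1) gives the primary aim as "To identify the barriers to establishing standardized SSI prevention practice". The secondary aims include variation by financial system and economic classification.
- Questionnaire development (2.3) states: "Data will be collected on participant surgical specialty, operative grade, country of practice and financial healthcare system of practice". It places the draft survey in Supplementary Material 1, which is not among the documents shown.

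**The concern.** The article names two reasons why answers may differ by region, then offers the origin of the questions as a remedy. Basing an item on a widely known guideline may make it recognisable everywhere. It does not alter which local or national policy governs the respondent's unit, or whether the hospital has the product.

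What is at stake is interpretation. A surgeon may report not using a measure by choice, because local policy says otherwise, or because it is unavailable. If a report starts from the position that regional and local-guideline differences are minimal, and reads variation as guidance not followed, the second and third reasons drop out. They are also natural candidates for the barriers that the primary objective sets out to identify.

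**Working it through.** The article states no figure on this point, so there is none to reproduce. The check is mainly one of consistency.

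**Step 1: does the inference hold?** Premise: the questions come from internationally recognised guidelines. Conclusion: regional discrepancies and local-guideline differences are small. The premise describes the instrument; the conclusion describes the respondents' circumstances. Nothing in the text links the two.

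**Step 2: does the rest of the article agree?**

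| Section | What it implies | Compatible with the claim? |
|---|---|---|
| Limitations, just before the claim | Local guidelines and access may differ by region | No; this is the limitation the claim is meant to answer |
| Introduction | The three guidelines differ from one another | No; sources that disagree cannot harmonise local guidance |
| Discussion, skin antisepsis | Specific advice varies | No |
| Discussion, rationale | Guidelines are inconsistent | No |
| Objectives; Discussion | Variation by economic class and country is to be studied | No; it is a target of measurement |
| Limitations, next paragraph | Variation means guidance is not followed | Leaves out the two explanations just conceded |

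**Step 3: how large a difference could access alone produce?** Every input here is an assumption. Observed use = use given availability × availability.
- Use given availability: 70% in both economic groups.
- Developed settings, availability 100%: 0.70 × 1.00 = 0.70.
- Developing settings, availability 80%: 0.70 × 0.80 = 0.56, a gap of 0.14.
- Developing settings, availability 60%: 0.70 × 0.60 = 0.42, a gap of 0.28.

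**Step 4: would a test of reported use flag such a gap?** Second set of assumptions: 80% use given availability in both groups, availability 95% in one group, 200 independent unweighted respondents per group, two-sided 5% test. The first group's observed use is 0.80 × 0.95 = 0.76. With z = (|p1 − p2| − 1.96·SE0)/SE1, where SE0 is the pooled and SE1 the unpooled standard error, the probability of a significant result is Φ(z).
- Availability 90% in the other group: 0.80 × 0.90 = 0.72; probability 0.15.
- Availability 80%: 0.80 × 0.80 = 0.64; SE0 = √(2 × 0.70 × 0.30/200) = 0.0458; SE1 = √((0.76 × 0.24 + 0.64 × 0.36)/200) = 0.0454; z = (0.12 − 0.0898)/0.0454 = 0.66; probability 0.75.
- Availability 60%: 0.80 × 0.60 = 0.48; probability above 0.99.

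With use given availability varied from 60% to 90%, the range is 0.09 to above 0.99. A comparison of reported use alone can therefore show a difference in which surgeons' choices play no part.

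**The case against.** The strongest reply is that the quoted sentence is hedged, does not name access to resources, and may mean only that the questions are applicable everywhere. Questionnaire development does say that only general, widely applicable measures will be included. On that reading there is no clash with the aim of finding variation. This stands in part: the sentence does not expressly withdraw the admission about access. It does name local-guideline differences, though, and applicability of the questions would not answer the limitation it follows.

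A reader might also infer that the survey cannot separate lack of access or local policy from choice, so that the economic comparison fails. The documents do not support this:
- The items are in a supplement that is not shown, and the list of respondent characteristics is not an inventory of questions.
- The primary objective is barriers, and multi-select, free-text and adaptive items are planned.
- Country is recorded, so national guidance could be examined in part.
- The economic objective is to identify variation, not to attribute its cause. Lower use due to lack of access is still a real difference in practice between systems.

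Finally, the numerical gaps are products of assumed inputs. They show direction and possible scale, not an error of that size in this survey.

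**Conclusion.** The point holds as one of reasoning and interpretation. The mitigation claim is unsupported and conflicts with the article's own account of the guidelines and its aims. The non-adherence reading that follows carries the omission into what the survey would conclude. The descriptive comparison across financial systems and economic classes is not invalid in itself; the explanation given for its differences is at risk.

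No size can be taken from the documents. The 14 to 28 points and the probabilities above are illustrations that assume identical choice given availability and unequal availability. Whether the questionnaire already captures governing guidance and availability is unknown. The text correction is needed whatever it contains.

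**What to change.** 1. Delete the sentence claiming that regional and local-guideline differences are kept to a minimum.
2. State instead that local guidance and access to resources remain expected explanations of regional and economic differences.
3. Reword the next paragraph so that variation may reflect non-adherence, disagreement between guidelines, local policy or lack of access.
4. During the pilot rounds, check that the questionnaire records the guideline or policy governing SSI prevention in the respondent's unit and whether each measure is available. Only if it does not, add one guideline item and an option for a measure not available in the respondent's hospital. Then report use both overall and among those with access.

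Items 1 to 3 are text edits. Item 4, if needed, lengthens completion slightly and means adding a response option across the prevention items. Under Questionnaire development, an added question counts as a major alteration that needs a unanimous, documented committee decision. The planned validation rounds are the place to make it.
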